## Abstract

**Background:**

Evidence indicates participation in a diabetes self-management education and support program improves self-care behaviors and hemoglobin A_1c_. Language and cultural differences may be barriers to program participation resulting in ineffective self-management, but these factors can be addressed with appropriate interventions. Given the high health care costs associated with diabetes complications, we developed a multicomponent, culturally tailored Self-Management Mobile Health Intervention for US Vietnamese With Diabetes (SMart-D).

**Objective:**

This study aims to evaluate the SMart-D intervention’s feasibility, acceptability, and effectiveness with intentions to scale up the intervention in the future. This mixed methods study incorporates the Reach, Effectiveness, Adoption, Implementation, Maintenance framework to evaluate the intervention.

**Methods:**

This stepped wedge randomized controlled pilot study will be conducted over 2 years in collaboration with primary care clinics. Eligible participants are patients with type 2 diabetes who are receiving health care from participating clinics. Clinics will be randomly assigned to an implementation date and will begin with patients enrolling in the control period while receiving standard care, then cross over to the intervention period where patients receive standard care plus the SMart-D intervention for over 12 weeks. Focus groups or interviews will be conducted with clinicians and patients after study completion. Qualitative data will be analyzed using NVivo. Outcomes on self-care behavior changes will be measured with the Summary of Diabetes Self-Care Activities scale and clinical changes will be measured using laboratory tests. A generalized linear mixed-effect model will be used to compute time effect, clustering effect, and the interaction of the control and intervention periods using SAS (version 9.4; SAS Institute).

**Results:**

We hypothesize that (1) at least 50% (n=5) of eligible clinics and 50% (n=40) of eligible patients who are invited will participate, and at least 70% (n=56) of patients will complete the program, and (2) patients who receive the intervention will have improved self-care behaviors and clinical test results with at least 75% (n=60) of the patients maintaining improved outcomes at follow-up visits compared with baseline, and participants will verbalize that the intervention is feasible and acceptable. As of August 2023, we enrolled 10 clinics and 60 patients. Baseline data results will be available by the end of 2023 and outcome data will be published in 2025.

**Conclusions:**

This is the first Vietnamese diabetes self-management education and support intervention that leverages mobile health technology to address the barriers of language and culture differences through collaboration with primary care clinics. This study will provide a better understanding of the implementation process, demonstrate the potential effectiveness of the intervention, accelerate the pace of moving evidence-based interventions to practice among the US Vietnamese population, and potentially provide a replicable implementation model that can be culturally adapted to other non-English speaking ethnic minorities.

**International Registered Report Identifier (IRRID):**

DERR1-10.2196/48585

## Introduction

Diabetes is a leading cause of death in the US Vietnamese population [1]. The term US Vietnamese will be used hereafter to indicate Vietnamese individuals living in the United States. Members of racial and ethnic minority groups are at an increased risk for developing type 2 diabetes (T2D) and experiencing complications from this disease [2]. After being diagnosed with T2D, individuals face many physical, emotional, and social challenges including the need to know about the strict diet and medication regimen and necessary lifestyle changes [3].

Nutrition is often the focus of self-management among US Vietnamese with diabetes, and little focus is placed on medication, blood glucose monitoring, risk reduction behaviors, or personal strategies for health promotion [4-6]. Self-management and health behaviors are influenced by cultural beliefs, practices, and availability of resources [7]. Ineffective self-management can lead to complications and increased health care costs. Glycemic control can reduce the risks of diabetes complications, but few resources are available to educate and support self-management among US Vietnamese. Despite the capability of improving health behaviors with evidence-based interventions, efforts to adapt and disseminate linguistic and culturally appropriate diabetes self-management education and support (DSMES) are lacking among this group.

Nguyen and Edwards [6] reported that linguistic and cultural differences as well as transportation issues are the main barriers to participating in existing DSMES programs among study participants. Many US Vietnamese living with T2D receive information from family, friends, and others diagnosed with diabetes for knowledge and decision-making around self-care [6]. Without formal DSMES, knowledge gained from informal education may negatively influence self-care behaviors. Low diabetes literacy hindered effective disease self-management, which is a striking finding among the participants that was revealed in every interview [6]. A needs assessment survey identified the community’s desire and need for formal diabetes education and support to be offered in the Vietnamese language in Oklahoma [8]. Studies showed that having limited English proficiency reduced the ability of study participants to obtain appropriate information to manage chronic conditions, such as heart disease and diabetes [9,10].

The 2022 National Standards for Diabetes Self-Management Education and Support [11] emphasized the need to provide services that embrace cultural differences, address social determinants of health, and use technological engagement platforms and systems. These National Standards cited strong evidence supporting DSMES delivery through digital, telehealth, telephone, SMS text messaging, and web-based or mobile phone app [11].

Nguyen et al [12] conducted a systematic review of intervention studies focused on improving health behaviors and health care services using mobile technology among the Vietnamese population and found the main device used was mobile phones. These devices were used for patient remote monitoring, assessment, or counseling for health behavior change through SMS text messaging, internet access, email, and videos. SMS text messaging was most frequently used as the primary intervention, which is consistent with many studies that have evaluated the usage of mobile health (mHealth) to support lifestyle and health behavior changes in other populations [13-16]. Using SMS text messaging to provide health education and monitor chronic diseases was feasible and acceptable mainly due to the low cost and easy operation of SMS text messaging [12]. However, the feasibility and acceptability of SMS text messaging to provide education and support among US Vietnamese patients is unknown and thus the aim of this study’s protocol.

In response to the burden of diabetes and the need to afford an opportunity for US Vietnamese with T2D an intervention that meets the National Standards [11], this Self-Management Mobile Health Intervention for US Vietnamese With Diabetes (SMart-D) study protocol will provide linguistically and culturally relevant diabetes education, health behavior change support, and emotional support through secure mHealth technology to help patients understand the disease process and gain skills to manage their condition. This protocol aims to describe a pilot study to test the acceptability and feasibility of the SMart-D intervention, determine the effectiveness, and assess its sustainability using the Reach, Effectiveness, Adoption, Implementation, Maintenance (RE-AIM) framework to measure outcomes. Focus groups or individual interviews will be conducted at program completion to assess intervention acceptability and participant experiences as well as perceived barriers to sustaining the behavior change.

## Methods

### Study Design

This study is a stepped wedge randomized controlled pilot study to implement a multicomponent intervention among US Vietnamese with T2D. The stepped wedge design allows the practical staggering of intervention delivery while enabling all participants to receive it. The intervention, incorporating both synchronous and asynchronous components over 12 weeks, is based on the patient empowerment and Health Belief Model and intends to target the unique needs of Vietnamese-speaking patients. Participants will receive a print booklet covering self-management strategies, daily mHealth SMS text messaging to promote self-care and enhance self-efficacy, and weekly nurse calls to coach and provide support for self-management goals. Offering these ongoing contacts will help to motivate participants to follow the care plan and engage in better self-management.

After the 12-week intervention, participants will opt to accept or decline a low dose of 1 monthly SMS text message and 1 monthly nurse call alternating biweekly for the next 9 months. This study will evaluate pre- and postintervention measures at 3, 6, 9, and 12 months from baseline. This framework will allow a comparison of outcomes between the standard care and intervention period as well as between baseline and follow-up data. To ensure the high quality of this pilot, this study will follow the SPIRIT (Standard Protocol Items: Recommendations for Interventional Trials) 2013 checklist [17,18].

### Intervention Components

The intervention has 3 components: print materials, mHealth SMS text messages, and nurse coaching telephone calls. Print education materials and follow-up telephone calls have been shown to be incrementally effective on their own [19-23]. Combining these components along with mHealth SMS text messaging may achieve a more significant effect. All 3 intervention components were assessed for usage and usability by piloting the components with 2 nurses and 4 Vietnamese individuals with T2D. Modifications to the intervention components were made based on the participants’ feedback.

All participants will receive a copy of printed materials entitled Small Change, Big Impact for People with Diabetes, which covers 8 chapters focusing on patient-centered strategies and incorporating cultural foods and practices. The content focuses on the day-to-day activities of living with diabetes with respect for the US Vietnamese individual’s life experiences helping participants (1) understand diabetes, (2) monitor blood glucose, (3) stay physically active, (4) cope with the diagnosis, (5) make healthy food choices, (6) understand Eastern and Western medications, (7) manage hypo- or hyperglycemia, and (8) prevent diabetes complications. The education content incorporates the Association of Diabetes Care and Education Specialists framework [24] and materials developed by the Centers for Disease Control and Prevention [25] diabetes resources and were adapted for cultural relevancy. All printed materials are available in Vietnamese and English language, side-by-side, to help participants learn the terminologies to communicate with their providers.

An mHealth SMS text message will be used to deliver educational content in the Vietnamese language via video, audio, and SMS text messages based on a schedule when specific criteria are met. The prerecorded videos are embedded in the SMS text messages and feature a registered dietician consulting with participants on developing a healthy eating plan that incorporates Vietnamese food and a pharmacist demonstrating insulin injection and self-monitoring of glucose. The secure mHealth platform will enhance both accurate, timely data collection across sites and ensure secure data transmission. During the 12-week intervention at least 1 message will be sent daily; up to 6 messages may be sent depending on the participants’ responses. If a participant does not respond to messages for 7 consecutive days, the coach nurse will assess any technical issues during the routine weekly calls. After the 12-week intervention, messages will be sent at a lower dose once monthly for the remaining follow-up period to allow continuing engagement with participants as they desire.

Participants will have a telephone coaching call with a Vietnamese-speaking nurse once per week during the 12-week intervention period. The day and time of these phone calls will be arranged between the participant and the nurse. Every week, participants will be encouraged to set one or more goals related to the scheduled lesson. During these coaching calls, the nurse will follow a script and use a motivational interviewing approach [26,27] to review participants’ goals and identify barriers, review status on self-management strategies, help participants build a capacity to problem solve, improve self-efficacy, and support health behavioral change. The use of a motivational interviewing approach by the coach nurse will encourage each participant’s intrinsic motivation to engage in self-care, change health behaviors, and improve their glycemic control [28]. Using a checklist, the nurse will document the content of each call and emphasize key educational topics including discussion of weekly goal attainment, discussion of barriers if the goal is not met, setting of goals for next week’s lesson, and provision of the opportunity to obtain personalized feedback if participants experience any challenges, and address concerns.

### Patient and Public Involvement in Intervention Development

The SMart-D intervention was developed with substantial engagement with the Vietnamese community of Oklahoma, including leaders of the Asian District Cultural Association, faith-based leaders, health care professionals, and people with T2D. This 23-member group served as an advisory board for over a 1-year period and highlighted the need to develop a feasible and appropriate study design as well as the need to incorporate language and culture-relevant information [29]. By incorporating the Health Belief Model, this SMart-D intervention emphasized the need to reduce diabetes complication risks and motivated participants to take into account the central concept of risk, thus encouraging health behavior change [30]. Accordingly, both Vietnamese language and cultural practices are strong components of this intervention, and using the stepped wedge design allowed all consented participants to receive the intervention. In addition, the intervention was preliminarily tested with a group of targeted individuals prior to implementation to ensure the usage and usability of the education content and method of delivery. After this study is completed, reports will be made available to clinics and patients in the form of a newsletter as well as a scheduled in-person seminar where the research team will describe findings with each individual clinic.

### Study Procedures

#### Inclusion or Exclusion Criteria

There are 2 levels of inclusion and exclusion: clinics and patients. Clinics are eligible if they currently serve more than 5 US Vietnamese adults diagnosed with T2D. T2D patients who identify as Vietnamese adults and receive health care at a participating primary care clinic will be eligible. Patients must be 18 years of age or older, diagnosed with T2D, able to provide verbal or written consent in English or Vietnamese, able to speak or read Vietnamese, and possess or have access to a mobile phone.

The exclusion criteria at the clinic level are those clinics that currently serve fewer than 5 US Vietnamese patients with T2D. At the patient level, individuals younger than 18 years of age, individuals visiting the United States as tourists, those with cognitive impairment, those unable to provide consent in English or Vietnamese, and pregnant women are excluded as pregnancy affects diabetes care differently at each trimester [11]. Patients will be terminated early if they become pregnant or explicitly refuse to have blood drawn as ordered by their physicians.

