#### Patient Recruitment and Consent Process

This study will recruit 80 patients from 10 clinics, approximately 8 patients from each clinic. We expect to have approximately 5 to 6 patients complete this study from each clinic giving a 70% (n=56) study completion rate. The power calculation was conducted by using the linear mixed effect modeling of the R (R Foundation for Statistical Computing) package “*swdpwr*,” which gives power of 0.95 for the alternative hypothesis treatment effect change of 0.005 (2-sided type I error 0.05). The recruitment strategy includes a letter and flyer to be sent by the clinics with the research team’s contact information. Study information will be provided to those who reach out to a research team member with their interest and an opt-out contact will be applied after 3 days of receiving the letter. A member of the research team will arrange a time to meet with eligible patients to discuss the option to participate in this study, complete the informed consent procedure, complete this study’s screener, and enroll them in this study if the individual is both eligible and interested. All patients will have the option of completing the consent and confidentiality forms in English or Vietnamese language. Upon full study enrollment, a member of the research team will collect baseline data.

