#### Data Collection

At enrollment, participants will complete the self-report demographic information survey, which will include age, gender, years of residence in the United States, and clinical information about their current treatment regimen to characterize the sample. For baseline data, participants will also complete the validated Summary of Diabetes Self-Care Activities (SDSCA) scale to measure self-care behaviors. The SDSCA scale, available in both English and Vietnamese languages, measures the participant’s management of diabetes in the last 7 days regarding diet, physical activity and exercise, blood glucose testing, foot care, and smoking. Participants answer 11 questions by indicating the number of days the behavior was followed in the past 7 days (0-7 days). In addition to self-reported behaviors, lab test results including triglyceride, low-density lipoprotein, high-density lipoprotein, hemoglobin A_1c_, and clinical assessments including BMI, blood pressure, and weight will be collected from their medical chart and entered into Research Electronic Data Capture (Vanderbilt University), a secure database. This information will be collected again at completion of the 12-week program and at 6 months, 9 months, and 12 months from baseline. Table 1 describes the timing of data collection and evaluation plan by the RE-AIM framework.

**Table 1 table1:** Data collection and evaluation plan using RE-AIM^a^ framework: assessment objectives, data, instruments, and timeline.

RE-AIM domain		Method	Baseline	Follow-ups (months after baseline)			
				3	6	9	12
Demographic patient information		Paper questionnaire	✓	N/A^b^	N/A	N/A	N/A
Clinic or facility information		Paper questionnaire	✓	N/A	N/A	N/A	N/A

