**Effectiveness: modification in self-care behavior and improvement in biological markers**							
	Changes in SDSCA^d^ scale	Paper questionnaire	✓	✓	✓	✓	✓
	Changes in triglyceride, LDL^e^, HDL^f^, HbA_1c_^g^, BMI, BP^h^, weight	Clinical assessment and lab results	✓	✓	✓	✓	✓
	Percentage of patients enrolled at end of study period	Enrollment data	✓	✓	✓	✓	✓

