The secondary outcomes are self-reported changes in behaviors and clinical test results, which will be compared to determine intervention maintenance and effectiveness. Repeated outcome measures will be assessed at 5 points in time. The translated and validated SDSCA revised scale [32] will be used to measure behavioral changes and assess 5 topics: diet, physical activity and exercise, blood glucose testing, foot care, and smoking. The average interitem correlations within scales were high (mean *r*=0.47) with the exception of specific diet; test-retest correlations were moderate (mean *r*=0.40). Correlations with other measures of diet and exercise generally supported the validity of the SDSCA subscales (mean *r*=0.23). Triglyceride, low-density lipoprotein, high-density lipoprotein, hemoglobin A_1c_, BMI, weight, and blood pressure will be used to measure clinical changes, which will be obtained from the participants’ medical records. Participants will be monitored for an additional 9 months via chart reviews and self-report using the SDSCA scale to determine whether any improvements observed at completion of the intervention will still be evident.

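### The rule that ends participation after a refused blood draw also stops later outcomes that need no blood, adding avoidable and possibly informative attrition

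*Protocol article*

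**What the plan says.** The rule stands in the protocol article under Inclusion or Exclusion Criteria: "Patients will be terminated early if they become pregnant or explicitly refuse to have blood drawn as ordered by their physicians". It carries no qualification. It does not say whether termination ends the intervention, the follow-up or both.

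Data Collection describes two kinds of outcome. The laboratory results are triglyceride, LDL, HDL and HbA1c. The others need no blood: "participants will also complete the validated Summary of Diabetes Self-Care Activities (SDSCA) scale to measure self-care behaviors", and "clinical assessments including BMI, blood pressure, and weight will be collected from their medical chart". All are to be repeated at the end of the 12-week program and at 6, 9 and 12 months. Outcome Measures puts both kinds to the same use: "The secondary outcomes are self-reported changes in behaviors and clinical test results, which will be compared to determine intervention maintenance and effectiveness".

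Patient Recruitment and Consent Process sets the numbers: "This study will recruit 80 patients from 10 clinics, approximately 8 patients from each clinic" and "We expect to have approximately 5 to 6 patients complete this study from each clinic giving a 70% (n=56) study completion rate". Table 1 lists, under Effectiveness, "Percentage of patients enrolled at end of study period". Data Analysis plans sequential multiple imputation for missing values and a summary of attrition. The Discussion sets the maintenance target at 75% (n=60).

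**The concern.** The rule reaches further than its trigger. A refused draw makes four laboratory values unobtainable, but it does not prevent a patient from completing a questionnaire or a chart from being read. If termination means leaving the study, every later outcome goes missing together, and the article gives no reason why the non-blood outcomes should stop.

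Two things are at stake. First, retention is itself a reported result of this pilot, and losses made by the protocol would be mixed with genuine dropout. Second, refusing an ordered diabetes test could plausibly be related to self-care or glycemic control, in which case the missing values are informative. Later SDSCA, weight and blood pressure values are the information that an imputation model could use to support the missing HbA1c and lipid values, and the rule stops their collection.

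**Working it through.** **1. The plan's own figures.** From Patient Recruitment and Consent Process and the Discussion:

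- Completion: 0.70 × 80 = 56, and 56 / 10 = 5.6 per clinic, which matches the stated 5 to 6.
- Losses allowed by that target: 80 − 56 = 24.
- Maintenance: 0.75 × 80 = 60. The base is all 80 enrolled; on the 56 expected completers, 75% would be 42, and 60 / 56 = 107%.

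Both targets are therefore set on all enrolled patients.

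**2. What a refusal makes unobtainable, and what the rule stops.**

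| Outcome | Source in Data Collection | Needs blood? | Stops if the patient leaves the study? |
|---|---|---|---|
| Triglyceride, LDL, HDL, HbA1c | Laboratory results | Yes | Yes |
| SDSCA (five topics) | Self-report questionnaire | No | Yes |
| Blood pressure, weight, BMI | Medical chart | No | Yes |

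The last two rows are the avoidable loss. Outcome Measures says that the nine months after the intervention rely on chart review and self-report, so these values would remain obtainable.

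**3. Illustrative size.** The article gives no refusal rate. Assume 5% to 10%:

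- Patients: 0.05 × 80 = 4 to 0.10 × 80 = 8.
- Share of allowed losses: 4 / 24 = 17% to 8 / 24 = 33%.
- Follow-up records: at most 4 visits each, so 4 × 4 = 16 to 8 × 4 = 32. This upper bound requires every refusal to occur before the first follow-up; later refusals lose fewer.

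**4. Possible effect on a mean change.** Assume also that refusers do 0.5 SD worse and that only retained patients are analyzed. The retained mean exceeds the all-patient mean by (proportion refusing) × (difference):

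- 0.05 × 0.5 SD = 0.025 SD
- 0.10 × 0.5 SD = 0.05 SD

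For scale, the simple standard error of a mean change with 56 completers is 1 / √56 = 0.13 SD before clustering. The assumed shift is less than half of that.

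**5. Possible effect on the maintenance proportion.** Suppose 75% of the retained patients maintain improvement:

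- 4 refusers: 0.75 × 76 = 57. This is 75% of those retained, but 57 / 80 = 71.3% of those enrolled.
- 8 refusers: 0.75 × 72 = 54. This is 75% of those retained, but 54 / 80 = 67.5% of those enrolled.

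Counted as failures over 80, terminated patients lower the proportion. Left out, they can raise it if they would have done worse. The direction depends on a handling rule that the article does not state.

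**The case against.** The strongest reply is that the article says very little on this point and that a reader can infer too much. Four stronger readings are tempting, and the documents support none of them.

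- *That the refusers' data are discarded.* No section deletes values collected before termination. At most, later values are lost.
- *That refusers are removed from the effect and maintenance estimates.* No section excludes them. Data Analysis plans multiple imputation, and the targets of 56 and 60 are both counted on 80.
- *That the rule removes the least engaged patients, or acts differently in control and intervention periods.* The article follows engagement through responses to texts and nurse calls. It does not link engagement to blood draws or give refusal rates by period.
- *That the results are biased upward.* This needs both an assumed difference between refusers and others and an assumed way of handling them. On a base of 80, the loss could as easily lower the maintenance figure.

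The trigger is also narrow: an explicit refusal of an ordered draw, not a missed or unordered test. And a condensed article may leave the handling of terminated patients to the full protocol or analysis plan.

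All of this stands, and it limits the point. It does not remove it. The concern rests on a rule that the article states without condition, not on an omitted detail. The rule stands beside pregnancy, itself an exclusion criterion, in the eligibility section, so leaving the study is its natural reading. Imputation answers the charge of removal, but not the avoidable loss of the values on which imputation could draw.

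**Conclusion.** The point holds in a limited form. Read as study termination, the rule ends later collection of SDSCA, blood pressure, weight and BMI for a reason that affects only four laboratory outcomes. It creates attrition that counts against the 70% (n=56) target and need not occur. The loss may be informative, and imputation under missing at random would not necessarily correct it.

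The size is unknown. The 4 to 8 patients and the 0.025 to 0.05 SD shift rest on an assumed refusal rate and, for the shift, on an assumed 0.5 SD difference and an analysis of retained patients only. They show that the effect on a mean is probably small beside sampling error in a pilot, while the effect on the retention count could be noticeable. The direction of any bias cannot be determined from the documents. The change is worth making because it is cheap and reduces missing data, not because bias has been shown.

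**What to change.** Amend the sentence under Inclusion or Exclusion Criteria, for data collection only, to state that after an explicit blood-draw refusal:

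- laboratory values are recorded as missing from that date;
- SDSCA and chart-based blood pressure, weight and BMI continue to be collected on the planned schedule, with the patient's consent;
- the patient stays in the analysis and in the 80-patient denominators for completion and maintenance.

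Whether intervention contact continues after a refusal is left to the investigators, and nothing is proposed on the pregnancy criterion.

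The cost is one sentence, with no new procedures, since the questionnaire and chart review are already planned. The downside is that somewhat more missing laboratory data will be reported among patients who remain in follow-up.
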